## Abstract

**Background:**

Obesity is a global public health issue. Having a BMI of 30 kg/m^2 ^or more (classifying a person as obese) at the start of pregnancy is a significant risk factor for maternal and fetal morbidity. There is a dearth of evidence to inform suitable inteventions to support pregnant women with a BMI of 30 kg/m^2 ^or more. Here we describe a study protocol to test the feasibility of a variety of potential healthy lifestyle interventions for pregnant women with a BMI of 30 kg/m^2 ^or more in a community based programme.

**Methods/Design:**

Four hundred women will be approached to attend a 10-week community lifestyle programme. The programme will be provided as a supplement to standard antenatal care. The programme is multi-faceted, aimed at equipping participants with the skills and knowledge needed to adopt healthy behaviours. The social (cognitive) learning theory will be used as a tool to encourage behaviour change, the behaviour change techniques are underpinned by five theoretical components; self-efficacy, outcome expectancies, goal setting, feedback and positive reinforcement.

The main outcomes are pregnancy weight gain and caesarean section rate. Other important outcomes include clinical outcomes (e.g., birth weight) and psychological outcomes (e.g., well-being). Secondary outcomes include women's experience of pregnancy and health care services, amount of physical activity, food intake and the suitability of the intervention components.

A prospective study using quantitative and qualitative methods will inform the feasibility of implementing the community lifestyle programme with pregnant women with a BMI of 30 kg/m^2 ^or more. Mixed methods of data collection will be used, including diaries, focus groups/interviews, pedometers, validated and specifically designed questionnaires, a programme register, weight gain during pregnancy and perinatal outcome data.

**Discussion:**

Findings from this current feasibility study will inform future interventions and NHS services and add to the evidence-base by providing information about the experiences of pregnant women with a BMI of 30 kg/m^2 ^or more undertaking a community lifestyle programme. The study will lead on to a randomised control trial of a suitable intervention to improve the pregnancy outcomes of this target group.

**Trail Registration:**

ISRCTN29860479.

## Background

A body mass index (BMI) of 30 kg/m^2 ^or more is classified clinically as obese, a BMI of 35 or more is morbidly obesity and a BMI of 40 or more indicates extreme obesity (World Health Organisation, 1998). Obesity is a global epidemic [1] and is high priority for Governments around the world. For example, in the United States the prevalence rate of obesity for over 20 year olds was 34% in 2005-2006 [2]. In England, two-thirds of adults and one-third of children are either overweight or obese and predictions suggest this could rise to almost nine in ten adults and two-thirds of children by 2050 [3].

Research from around the world has highlighted that maternal obesity carries significant risks to both mother [e.g. [4,5]] and baby [e.g. [6-8]]. In the US, the percentage of women who are overweight (BMI of 26 or more) at the pre-pregnancy stage has been increasing for over 20 years [9]. In one area of England, the percentage of pregnant women who have a BMI of 30 kg/m^2 ^or more at conception increased from 9% to 16% over a 15-year period [10]. The impact of BMI on pregnancy outcomes in the UK was highlighted in the recent triennium review into maternal mortality highlighted maternal obesity as an 'obstetric risk factor'; 27% of women who died from direct and indirect causes in the UK had a BMI of 30 kg/m^2 ^or more [11].

Excessive weight gain has been found to increase the risk of complications in pregnancy and a low weight gain during pregnancy has been suggested as beneficial for obese women [12]. The Institute of Medicine (IOM) provides ranges of recommended ranges of weight gain for women during pregnancy. These recommended ranges are dependent on the woman's weight at the start of the pregnancy and were revised in 2009. Women with a BMI of more than 30 kg/m^2 ^should not exceed a weight gain of 5-9 kg (the 1990 report stated 7 kgs) during their pregnancy [13]. The IOM's recommended weight-gain ranges have been found to be associated with the best outcomes of pregnancy for mothers in the USA [14]. However, in the UK there is little evidence to support these weight gain recommendations and no guidelines are in place.

As a consequence of this association with adverse outcomes of pregnancy, we are keen to conduct research to improve the health of pregnant women who have a BMI of 30 kg/m^2 ^or more. Although pregnancy has been suggested as an optimal time for intervention by health care professionals involving health promotion messages [15] and national recommendations have suggested healthy pregnancy advice should be provided before 12 weeks gestation [e.g. [16]]. Little guidance is provided for health care professionals for work with this group (NICE guidelines are expected in mid-2010) and as a result there is minimal support, care pathways and services for pregnant women who have a BMI of 30 kg/m^2 ^or more. A systematic review of weight maintenance interventions concluded there is minimal evidence to inform maternal obesity strategies [17].

There is insufficient evidence to inform the design of an effective and appropriate intervention for pregnant women with a BMI of 30 kg/m^2 ^or more as there is a dearth of evidence--based and theory-based research on this target group. The recent NICE commissioned evidence reviews of dietary and/or physical activity interventions for weight management in pregnancy [18] and post-partum [19] found a small number of robust studies in the UK. They concluded that there is 'inconsistent and inconclusive evidence' on the effectiveness of weight management interventions in pregnancy (p.12 [18]).

A recent review by the Kings Fund highlighted several theories of behaviour change (e.g. stages of change model), psychological constructs (e.g. self-efficacy) and types of interventions (e.g. goal-setting) that have been successfully applied to the up-take of physical activity and eating a healthy diet in the general population [20]. The need for community and individualised intervention studies for weight maintence in pregnancy and post-partum have been the conclusions of several studies [21,22] and approaches to lifestyle and behaviour change which ignore the wider social context are likely to have limited success [23,24]. Lifestyle programmes and structured physical activity programmes have equally been found to increase health benefits in healthy sedentary adults [e.g. [25]]. Therefore, it is important when addressing obesity to target numerous health behaviours that contribute to weight gain; physical activity, healthy eating and emotional well-being. In addition, interventions must have theoretical underpinnings such as those listed in the Kings Fund report.

This paper outlines the design (rationale and theoretical-framework) of a community lifestyle programme study which may offer benefit to pregnant women with a BMI of 30 kg/m^2 ^or more by improving their own and their babies' physical and psychological well-being. Our community lifestyle programme will address numerous behaviours associated with obesity (e.g. physical activity, emotional well-being and food-intake) and will equip participants with the necessary skills and knowledge to incorporate healthy behaviours into their everyday lives (social (cognitive) learning theory [e.g. [26]] will be used as a tool to encourage behaviour change [27]). The feasibility of this lifestyle programme will be evaluated so as to assist researchers in the design of future studies and programmes and may be subjected to a trial at a later date.

## Methods/Design

This is a prospective study, using mixed-methods of data collection to inform the feasibility of implementing a community lifestyle programme with pregnant women with a BMI or 30 kg/m^2 ^or more in the Greater Manchester areas of Bolton and Oldham. Randomised controlled trials are considered the gold standard when assessing interventions [28]. However, one has to be sure that the intervention is of the highest standard, and acceptable to those who will be receiving it prior to proceeding to a randomised controlled trial. There is currently no evidence suggesting the optimum intervention for this group of women, nor is there any evidence of intervention acceptability. Therefore, following the advice of the Medical Research Council (MRC) framework for a complex intervention [29] we believed it imperative that a feasibility study was conducted prior to any such trial. Our approach to programme development is one which allows fluidity, i.e. the programme will be adapted contemporaneously following feedback and review.

### Research team

The core research team consists of the principal investigator (Professor of Midwifery), project manager (health psychologist) and two research midwives. An Advisory Board of leading experts (clinicians and academics) in obesity and pregnancy meet twice a year during the study. A Lay Advisory Group; four pregnant women with a BMI or 30 kg/m^2 ^or more in Bolton and four pregnant women with a BMI or 30 kg/m^2 ^or more in Oldham, will meet three times throughout the first programme.

### Setting

The study is being conducted in England, in the Greater Manchester areas of Bolton and Oldham. The two areas have similar ethnic diversity (predominantly white; Bolton - 90% and Oldham - 86% with minority ethnic groups concentrated in small areas), level of health (lower than the National average), deprivation (among the most deprived areas in England) and pregnancy data (maternal obesity is found in approximately 16% of the women delivering) [30].

### Sample

Four hundred pregnant women with a BMI of 30 kg/m^2 ^or more will be approached to participate in the study (200 from each area). Women will be excluded from participation in the study if they have a BMI of less than 30 kg/m^2^, are aged under 18, intend to move in the next three months, take weight control medication or if they have any cautions for starting exercise (this will be determined using the Revised Physical Activity Readiness Questionnaire (PARQ) [31]) and the Royal College of Obstetricians and Gynaecologists (RCOG) recommendations [32]). Their obstetrician will be consulted in cases where the PARQ or RCOG guidelines indicate concerns. Each participant's General Practitioner (GP) will be sent a letter outlining the involvement in the study. The sample size is determined pragmatically by the need to gain sufficient experience of the intervention over a range of settings and participants and thus test feasibility on a realistic basis. 200 participants is more than adequate to estimate standard deviations and 10-12 groups will allow us to estimate the intraclass correlation for the design of future studies. Formal comparisons are pre-post measures where 200 participants will give 80% power to detect small changes of 0.2 or larger, expressed as standardised effect sizes in terms of the intra-patient standard deviation (80% power, paired t-test). The major obstetric outcomes (caesarean section and low birth weight) have expected incidence rates of around 20% [6] and will be estimated with a 95% confidence interval width of approximately 5%, allowing large effects to be detected in comparison with audit data.

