### Outcomes

The main outcome of interest is pregnancy weight gain. Other important clinical outcomes include birth weight, mode of birth and method of infant feeding at hospital discharge. Important psychological outcomes include self-efficacy, well-being and goal attainment. Secondary outcomes include women's experience of pregnancy and health care services, amount of physical activity, food intake and the suitability of the intervention components.

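### The stated 95% confidence interval width of about 5% for caesarean section and low birth weight is less than half the true width (about 11 points) at 200 participants

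*Protocol article*

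**What the plan says.** The Sample section of the protocol article describes the sample size as pragmatic and then says what it will deliver. Two of these statements name the number of participants: "200 participants is more than adequate to estimate standard deviations", and, for the pre-post comparisons, "200 participants will give 80% power to detect small changes of 0.2 or larger" in standardised units.

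The obstetric outcomes follow directly: "The major obstetric outcomes (caesarean section and low birth weight) have expected incidence rates of around 20" per cent, and these "will be estimated with a 95% confidence interval width of approximately 5%, allowing large effects to be detected in comparison with audit data". No other sample size is given for this sentence, and nowhere does the article say that width means half-width or a ± margin.

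The Abstract names the caesarean section rate as a main outcome beside pregnancy weight gain. The Outcomes section names weight gain alone as the main outcome and continues: "Other important clinical outcomes include birth weight, mode of birth and method of infant feeding at hospital discharge". Low birth weight as a yes/no outcome appears only in the Sample section.

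**The concern.** The width of a confidence interval ordinarily means the upper limit minus the lower limit. Read that way, the sentence promises that a 20% rate will be known to about ± 2.5 percentage points. A sample of 200 cannot give that for an event this common.

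This is the only statement of precision for the obstetric outcomes, and the protocol draws a conclusion from it about comparison with audit data. The study is also intended to lead to a randomised trial, so a reader could credit its caesarean rate with about twice the precision it will have. What counts as a large, detectable effect depends on the same figure.

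**Working it through.** **Inputs, all from the Sample section**
- Participants: n = 200. This is the number in the sentences on standard deviations and on pre-post power. As a check that it is the design size, a paired t-test with n = 200 and a standardised effect of 0.2 has power 80.4%, which reproduces the stated 80%.
- Upper bound: n = 400, the number of women to be approached. It is relevant because the Recruitment section allows clinical outcome data to be used, with consent, from women who do not join the programme.
- Expected rate: p = 0.20. Confidence level: 95%.

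**Attempt to reproduce the stated figure**

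Half-width = 1.96 × √(p(1 − p)/n); width = 2 × half-width.

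| n | Half-width (points) | Width (points) |
|---|---|---|
| 200 | 1.96 × √(0.16/200) = 5.54 | 11.1 |
| 400 | 1.96 × √(0.16/400) = 3.92 | 7.8 |

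At n = 200 the interval is 14.5% to 25.5%. The ratio to the stated width is 11.1/5 = 2.2.

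**Could another reading give a width of 5?**
- Other interval methods at n = 200: Wilson 11.0 points, Agresti-Coull 11.1, Clopper-Pearson 11.5.
- Other rates around 20% at n = 200: 9.9 points at 15%, 12.0 points at 25%.
- Lower confidence levels at n = 200: 9.3 points at 90%, 7.2 points at 80%.
- Rate at which n = 200 gives a width of 5 points: about 3.4%, far from 20%.
- Sample size for a width of 5 points: 1.96² × 0.16/0.025² = 983.4, so 984 women.
- Half-width reading: ± 5.5 points at n = 200. This is the only reading near the stated figure. A half-width of exactly 5 points needs 1.96² × 0.16/0.05² = 245.9, so 246 women.

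**What a large effect means at n = 200**

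The protocol gives no audit rate, so assume a fixed comparison rate of 20% and an exact two-sided 5% binomial test (at most 2.5% in each tail). The test rejects at 28 or fewer events, or at 52 or more.

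| True rate | Power |
|---|---|
| 12% | 0.84 |
| 13% | 0.71 |
| 28% | 0.76 |
| 29% | 0.84 |

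A fall is therefore detectable with at least 80% power at about 12%, a relative reduction of (20 − 12)/20 = 40%. A rise is detectable at about 29%.

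**Sensitivity, on assumptions not in the protocol**
- Clustering: the protocol expects 10 to 12 groups but gives no intraclass correlation. With a design effect of 1 + (200/g − 1) × ICC, for g groups, an assumed ICC of 0.01 gives a width of about 12 points and an assumed 0.05 gives about 15.
- Low birth weight: if its rate were 5% to 10% rather than 20% (an assumption), the width at n = 200 would be 6.0 to 8.3 points.

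**The case against.** The strongest reply is that one word is wrong and nothing in the design depends on it. Read as a margin of error, about 5% is 5.5% rounded down, so the underlying calculation was roughly right. The sample size was not derived from this precision. The formal comparisons are pre-post, and their power statement is correct. The text promises only that large effects can be detected, and a 40% relative fall is large, so the qualitative claim survives. Nor does the protocol say that the later trial would be sized on this interval; for future studies it names the intraclass correlation.

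Much of this stands. It limits the consequence and rules out any call for a larger sample. It does not make the sentence right: the protocol says width, never ±, and no sample size from 200 to 400 gives a width of 5 points.

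The reply is also fair on the side material. The clustering widths and the 5% to 10% rate for low birth weight rest on assumptions, and the source cited for the 20% is not at hand, so that rate is not shown to be wrong. Low birth weight can be derived from the listed birth weight, so the mismatch with the Outcomes section is one of definition. The main error depends on none of these.

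**Conclusion.** The stated precision is wrong as written. At 200 participants and a 20% rate, the 95% confidence interval is about 11 points wide (± 5.5), not about 5. This follows from the protocol's own figures and holds for every standard interval method tried. Mislabelling the half-width is the probable cause.

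The 11 points are a best case: they assume outcome data on all 200 women and no clustering by programme group. The detectable differences of about 12% and 29% further assume a comparison rate fixed at 20%, with no sampling error of its own. The error misstates the precision of an outcome that the Abstract calls main. It leaves the sample size and the pre-post power statement untouched.

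**What to change.** Replace the precision sentence in the Sample section with wording such as: *With 200 participants, a 20% rate will be estimated to within ± 5.5 percentage points (95% CI about 14.5% to 25.5%, width about 11 points). Against a fixed rate of 20%, only a fall to about 12% or a rise to about 29% could be detected with at least 80% power.* If the audit rate to be used differs from 20%, recompute the second sentence for that rate.

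Give low birth weight its own expected rate and interval, or replace it here with the birth weight outcome that the Outcomes section lists.

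The cost is a sentence or two of protocol text and a less favourable stated precision. No extra participants and no change of design are needed.

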### Outcomes

The main outcome of interest is pregnancy weight gain. Other important clinical outcomes include birth weight, mode of birth and method of infant feeding at hospital discharge. Important psychological outcomes include self-efficacy, well-being and goal attainment. Secondary outcomes include women's experience of pregnancy and health care services, amount of physical activity, food intake and the suitability of the intervention components.

### Recruitment

Approval has been gained from the NHS research ethics committee, the individual Primary Care Trusts' research and development departments (Pennine Acute Trust and Bolton NHS Hospitals Trust) and The University of Manchester.

Support from friends and family will be encouraged throughout the recruitment stage and the programme as it can be influential on women's participation in physical activity [33]. Language will be assessed on a one-to-one basis and translators employed where necessary. Recruitment is being predominantly carried out through the full time research midwives in antenatal clinics. Women are able to opt into the study at anytime after reading the invitation letter and receiving verbal information about the study. A screening sheet will be completed to identify their suitability (based on the exclusion criteria above) and will collect demographic details (e.g. ethnicity, age, marital status, level of education and area deprivation). If the woman is suitable for inclusion she will be asked by the research midwife to sign a consent form and a date for the initial session will be set. At the initial session, the research midwife will explain the details of the 10-week programme, ask them to complete the baseline questionnaire and give them the diary and pedometer. If a woman is not suitable for inclusion or she does not want to attend the lifestyle programme, she will be asked to complete a consent form to say that her screening data and clinical outcome data can be used.

### The 10-week lifestyle programme

The lifestyle programme will run for one and a half hours per week for 10 weeks and is supplementary to standard antenatal care. Women will be invited to the 10-week programme at any stage before 30 weeks gestation to ensure completion of the programme before their delivery.

Given the complexities surrounding the psychological and physical causes of obesity, a multi-component intervention is being used (as suggested by [12]). The programme will be interactive and cover several aspects of their lifestyle (e.g. physical activity, healthy eating and emotional well-being) and their children's well-being (attendance will be encouraged at some groups). Physical activity is an important aspect and will feature each week in the lifestyle programme. The RCOG clinical guidance, following a review of the available evidence around pregnancy and the post-partum period [31], concluded that, in most cases, 'exercise is safe for both mother and fetus during pregnancy.' There are also reports of psychological benefits of exercising for the mother [34,35].

Physical activity is generally low in pregnancy [e.g. [36]] but the reasons for this are not clearly understood. A recent study found that the main barriers (reported in 85% of cases) were intrapersonal (e.g. health-related) [37]. In addition, women are not currently being supplied with the message that physical activity during pregnancy is safe [38] only half of obstetricians discuss physical activity with pregnant women and those who do are likely to advise not to start exercise [39]. Physical activity will be discussed throughout the programme as it needs to be incorporated easily into peoples' everyday lives if they are to adopt it [40]. To achieve this, a trained and insured physical activity instructor will provide half an hour of activity each week in the intervention and will suggest exercises that the women can incorporate into their lifestyle.

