**Psychological variables**		

Self-efficacy	To increase the women's self-efficacy, so they are more motivated to make healthy changes to their lifestyle	Self-efficacy will be increased by: -Problem solving activities in 10-week programme (e.g. minor ailments in pregnancy pass-the-parcel) -Feedback and reinforcement through the group at the 10-week programme -Personal goal setting during 10-week programme - the setting of a realistic and short-term goal will increase experience of success

Outcome expectations	Develop realistic expectations about the benefits of improving their well-being (physical activity, healthy eating and emotional well-being - relaxation)	When setting their personal goal and in the questionnaires, they will be asked to think about the outcomes of any changes to their behaviour and the impact on their lifestyle. The barriers and facilitators of goal attainment will be discussed at the goal setting stage (week 1 of 10-week programme) and goal attainment stage (week 10 of 10-week programme) Baseline questionnaire and goal setting stage (week 1 of 10-week programme) will ask open questions on their expectations and views regarding behaviour change

Feedback	To provide constant feedback to the women throughout the programme to encourage the uptake of healthy behaviours and changes to their lifestyle	Feedback will take the form of changes to their lifestyle as recorded in their diary and involvement in the lifestyle programme (via health care professionals and other women in the group)

Positive reinforcement	Positive reinforcement will be received by women when they engage in healthy behaviours or changes to their lifestyle	Positive reinforcement will be offered to the women to increase their self-efficacy, this will occur through the other women in the group, the health care professionals and self-monitoring of their diary entries

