**Environmental variables**		

Access to health care	Women will be provided with information about other programmes and services that may be of relevance to them during their pregnancy and in the post-partum stage	Women will be provided with information about other programmes and services that may be of relevance to them during their pregnancy (e.g. one session in the 10-week programme is dedicated to signposting to other services). Additional activities (e.g. aquanatal class, supermarket tour and pampering session) will be offered to the women alongside the 10-week programme as taster sessions.

Self-efficacy is central to Social Learning Theory, unless a person believes that they can produce the desired outcomes through the behaviour they have little reason to act. Self-efficacy regulates motivation and determines the goals people set, their determination to meet their goals and the outcomes they expect. Self-efficacy can be increased by four processes. Firstly, if we experience successes then our self-efficacy rises. Each week the women will take part in small problem-solving activities which they can succeed at (e.g. pass-the-parcel game where women had to decide if pregnancy statements were true facts or myths). Secondly, our self-efficacy rises if we see those similar to ourselves succeed; the women will share experiences as a group so that they can share each others experiences and talk about the reasons for their successes and failure (reinforcement and feedback). The third process is through social persuasion, if we are persuaded verbally that we can do something then we are more likely to believe it. To encourage the women, they will receive educational sessions from health care professionals about their health behaviours and their goals for the programme will be discussed with a health psychologist. Finally, our somatic and emotional state influences our self-efficacy; positive mood enhances self-efficacy and makes us view fatigue more favourably. The women will be in the same group for the whole programme so will gain social support and feedback on their behaviour to provide an environment to foster positive mood. Social support has been shown to have a positive impact on our health [44].

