### Data Collection and analysis

Mixed-methods of data collection will be employed (Table 2 outlines the data collection and outcome measures); questionnaires including validated measures [31,49-51] and open questions (given out at baseline, the start of the 10-week programme, the end of the 10-week programme and at follow-up), diaries (completed from baseline to follow-up to provide detailed qualitative data) and focus groups at 4-6 weeks post-partum (interviews will be offered where attendance is not possible). The diaries will provide qualitative data daily insight into the women's feelings during pregnancy, behaviour change and any barriers and facilitators to this behaviour change. In addition, the women's weight gain during pregnancy (women will be weighed at their booking appointment at the end of their pregnancy) and clinical outcome data (e.g. type of birth and blood loss) will be examined. The focus groups will provide follow-up data about the women's views towards the programme after giving birth.

**Table 2 T2:** Data collection and outcome measures

	Recruitment (screening sheet)	Recruitment (baseline)	Start of 10-week programme	End of 10-week programme	10-week programme register	End of pregnancy	Follow-up questionnaire	Follow-up interview/focus group	Diary
Demographics	X								

Physical Activity Readiness Questionnaire (PARQ) - [31]	X	X							

Weight (weight gain during pregnancy and Body Mass Index [BMI])	X					X			

Pregnancy physical activity questionnaire (PPAQ) [49]		X	X	X			X		

Physical activity changes - barriers/facilitators to this change			X	X			X	X	X

Attitudes towards physical activity		X	X	X			X	X	X

Attitudes towards their pregnancy and baby		X	X	X			X	X	X

Food intake changes - barriers/facilitators to this change			X	X			X	X	X

Attitudes towards food intake		X	X	X			X	X	X

General Self-efficacy scale (GSES) [50]		X	X	X			X		

Well-being (W-BQ12) [51]		X	X	X			X		

Attitudes towards their weight			X	X			X		X

Experience of advice received about weight gain during pregnancy	X	X	X	X			X	X	

View of health care and treatment from health care professionals		X	X	X			X	X	X

Views and attitudes towards 10-week programme				X				X	X

Attendance at 10-week programme				X	X			X	X

Outcome expectations of factors influencing pregnancy		X	X	X			X	X	

Outcome expectations of study participation		X					X		

Goal setting			X						

Goal attainment - barriers/facilitators				X			X		X

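### The 30-week limit applies to invitation, not to session 1, so it does not ensure that late entrants finish ten weekly sessions before birth

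*Protocol article*

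**What the plan says.** The section on the 10-week lifestyle programme gives the rule and its purpose in one sentence: "Women will be invited to the 10-week programme at any stage before 30 weeks gestation to ensure completion of the programme before their delivery". The same section fixes the length: "The lifestyle programme will run for one and a half hours per week for 10 weeks and is supplementary to standard antenatal care".

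Other sections put steps between invitation and the first group session:

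- **Recruitment.** A screening sheet comes first. A suitable woman will then "sign a consent form and a date for the initial session will be set". At that initial session she completes the baseline questionnaire and receives the diary and pedometer.
- **Data collection and analysis.** Questionnaires are "given out at baseline, the start of the 10-week programme, the end of the 10-week programme and at follow-up", so baseline and programme start are separate time points. Table 2 gives them separate columns.
- **Theoretical framework, text after Table 1.** "The women will be in the same group for the whole programme". The Sample section plans 10-12 groups.

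The end of the programme is a measurement point. Table 1 refers to the "goal attainment stage (week 10 of 10-week programme". Table 2 schedules physical activity (PPAQ), self-efficacy (GSES), well-being (W-BQ12), goal attainment and programme views there. The planned quantitative analysis compares data before and after the programme.

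**The concern.** The article offers a guarantee, completion before birth, and derives it from a limit on the date of invitation. What decides completion is the date of session 1 of the group a woman joins, and no gestational limit is given for that date.

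If the guarantee fails, it fails selectively, in women who enter late and women who give birth early. Two results of the feasibility study are exposed:

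- The end-of-programme time point may be missing for these women. If it is collected after birth, it may not be comparable with measures taken in pregnancy, most obviously for a pregnancy physical activity questionnaire.
- A count of sessions attended may mix two different things: women who stopped coming, and women whose baby arrived while their group was still running. The first concerns acceptability. The second concerns scheduling.

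**Working it through.** **1. Calendar arithmetic.** Inputs from the article: latest invitation 29+6 (before 30 weeks) and ten weekly sessions. The first and tenth sessions are nine weeks apart. The wait between invitation and session 1 is not stated, so it is varied.

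Gestation at session 10 = 29+6 + wait + 9 weeks.

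| Wait | Session 1 | Session 10 | Ten full weeks counted |
|---|---|---|---|
| 0 weeks | 29+6 | 38+6 | 39+6 |
| 1 week | 30+6 | 39+6 | 40+6 |
| 2 weeks | 31+6 | 40+6 | 41+6 |

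The rule appears to rest on 30 + 10 = 40 weeks. That sum allows nothing for the steps between invitation and session 1, and nothing for birth before 40 weeks.

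**2. Chance of birth before session 10 (illustration).** The article gives no distribution of gestation at birth. Assumption: normal, mean m = 39 to 40 weeks, SD s = 1.5 to 1.8, in a woman undelivered at 30 weeks. With x the gestation at session 10 and Φ the normal distribution function:

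P = [Φ((x − m)/s) − Φ((30 − m)/s)] / [1 − Φ((30 − m)/s)]

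The terms in 30 are negligible: with m = 39 and s = 1.8, (30 − 39)/1.8 = −5. The extremes over the whole range for invitation at 29+6 are:

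| Wait | x | Lowest | Highest |
|---|---|---|---|
| 0 weeks | 38.86 | m = 40, s = 1.5: Φ(−0.76) = 22% | m = 39, s = 1.8: Φ(−0.08) = 47% |
| 1 week | 39.86 | m = 40, s = 1.5: Φ(−0.10) = 46% | m = 39, s = 1.5: Φ(0.57) = 72% |
| 2 weeks | 40.86 | m = 40, s = 1.8: Φ(0.48) = 68% | m = 39, s = 1.5: Φ(1.24) = 89% |

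**3. Earlier entrants, same assumptions.**

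- Invitation at 26 weeks: 0-1% with no wait. With two weeks x = 37, giving 2-13%.
- Invitation at 24 weeks: with two weeks x = 35, and the highest value is Φ((35 − 39)/1.8) = Φ(−2.22) = 1%. The range for waits of 0 to 2 weeks is about 0-1%.

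The shortfall is therefore concentrated in late entrants.

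**4. Bearing on the stated power.** The Sample section says "200 participants will give 80% power to detect small changes of 0.2 or larger" for a paired t-test. With two-sided alpha 0.05 (not stated, assumed) and 0.2 taken on the SD of the differences, 200 pairs give 80.4%, so the figure reproduces. It leaves little room for lost pairs: 190 pairs (5% lost) give 78.3%, 180 (10%) give 76.1% and 160 (20%) give 71.0%. These losses are illustrative and are not predictions of how many women will give birth before session 10.

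**5. What is not affected.** Table 2 takes weight and clinical outcomes at the end of pregnancy. PPAQ, GSES, W-BQ12 and goal attainment are repeated in the follow-up questionnaire. Programme views are also taken at the follow-up interview or focus group and in the diary. The register records attendance.

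**The case against.** The best reply is that this is one loose word in a condensed article on a pragmatic feasibility study whose programme is meant to be adapted as it runs. Several parts of that reply stand.

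- **The wait is inferred.** The fixed group, the separately dated initial session and the split between baseline and programme start all imply one, but no length is given. The sentence might also be read as entry to the programme before 30 weeks. Even so, with no wait the latest entrant has session 10 at 38+6, so the guarantee still fails. Only the larger percentages depend on the wait.
- **The percentages describe the latest possible entrant.** Most women may be invited much earlier.
- **Handling of women who give birth during the programme may be set out in the full protocol or analysis plan.** Its absence from the article is not criticised here. The point is that a stated rule does not yield the property stated for it.

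A reader might go further and infer that the psychological and activity measures exist only for women still pregnant at week 10, that attendance data are lost, or that the main outcome is compromised. The documents do not support any of these. The measures recur at follow-up, the register holds attendance, and pregnancy weight gain does not depend on reaching session 10. Nor does the article require the end-of-programme questionnaire to be completed in person or before birth. One time point is at risk for some women, together with the interpretation of the session count.

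**Conclusion.** The point holds in this limited form. A limit on invitation before 30 weeks does not ensure completion of ten weekly sessions in a fixed group before birth. This rests on calendar arithmetic from the article and is firm: session 10 falls at 38+6 at best for the latest entrant, and at 39+6 or 40+6 with a one- or two-week wait.

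The size is conditional. The ranges of 22-47%, 46-72% and 68-89% rest on an assumed distribution of gestation at birth and an assumed wait, and apply only to invitation at 29+6. The whole-sample effect cannot be computed, because the article gives neither gestation at entry nor waiting times. It would therefore be wrong to conclude that the comparison before and after the programme is materially biased; selective loss is plausible, and its extent is unknown. The matter should be corrected because it is cheap to do so and because attendance and end-of-programme results will inform the planned randomised trial.

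**What to change.** Reconcile the Recruitment section, the section on the 10-week programme and the fixed-group statement after Table 1. Either state the gestational limit at session 1 of the group the woman would join, with the value left to the sponsor, or keep the present rule and withdraw the word *ensure*.

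Whichever is chosen:

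- record gestation at session 1;
- code birth before session 10 as its own reason for non-completion, separate from drop-out;
- report attendance as sessions attended out of sessions held before birth, alongside the raw count.

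Moving the end-of-programme questionnaire to the last session before birth is not a workable substitute. That session cannot be identified in advance, and the amount of programme received before the measure would vary between women.

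The cost is a sentence in the protocol, one date and one extra code on the register. If the limit moves to session 1, a few late entrants may be lost or directed to an earlier group.
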